### Randomisation

Participants will be randomised after the baseline assessment. Randomisation will be achieved using computer-generated random numbers and randomly permuted block sizes of 4–8. The single centralised randomisation schedule will be undertaken by the NeuRA research studies coordinator with no involvement in the study and group allocation will be concealed from all study investigators and staff using consecutively numbered sealed opaque envelopes.

### Intervention group

Participants in the intervention group will receive fall prevention strategies based on their individual risk factors identified. The clinical researcher will pro-actively work with the older person to prioritise and facilitate implementation of the suggested intervention strategies.

#### ***Physical performance***

Strength and balance training will be recommended if the participant’s physical performance is thought to be a contributing factor as assessed using the measures outlined in Table 1. It is anticipated that the majority of the intervention group will be offered this intervention. If the participant lives within the catchment area of the Prince of Wales Hospital, the Otago Exercise Programme [34] will be delivered by the PACS service physiotherapist or nurse. The Post Acute Care Service is a State funded clinical program that aims to provide rapid assessment and support of people through a range of disciplines to prevent unnecessary hospital admission or facilitate timely hospital discharge. The Ambulance Service do not currently access this service. Participants will also be referred to local evidence-based exercise programs (not all delivered through health care) to ensure that they continue exercising on completion of the Otago Exercise Programme. Participants living outside the catchment area will be offered the Otago Exercise Programme delivered by a research physiotherapist.

#### ***Home safety***

Issues related to safety in the home environment will be referred to the PACS occupational therapist. Where participants are residing outside of the PACS catchment area, the clinical researcher will arrange for a community occupational therapist from the relevant local hospital to address the identified safety issues.

#### ***Visual impairment***

People with poor vision and no associated clinical diagnosis or recent visual assessment will be referred to their usual eye-care provider or a local optometrist for a visual assessment. Participants will also be offered the option of a home visit by a community optometrist, and the clinical researcher will arrange the referrals if required.

#### ***Home medication review***

Participants taking medications known to increase fall risk will be referred to their GP and encouraged to discuss the ongoing need for these medications. These medications include benzodiazepines, antidepressants, antipsychotics and opiate containing analgesic agents. A Home Medication Review will also be encouraged particularly where there is evidence of impaired cognition or reported difficulties taking medications. The GP will be contacted by the researcher to explain the nature of the project and a referral template will be faxed to the GP to minimise any additional work for GPs.

#### ***Falls, balance and bone health clinic or aged care clinic***

For participants with complex needs or multiple identified risk factors, a referral to the POW Falls, Balance and Bone Health Clinic or Aged Care Clinic will be organised. The GP will be contacted by the researcher to explain the nature of the project and a referral template will be faxed to the GP to aid with the referral process and minimise additional work for the GP.

### Control group

Participants randomised to the control group will receive a written copy of the risk factors identified during the baseline assessment but will not be provided with any additional support to implement the recommendations. They will be encouraged to discuss the results of the baseline assessment with their GP or other relevant health care provider.

### Outcome measures

The primary and secondary study outcome measures are listed in Table 1. All participants will be followed for a total of 12 months after the baseline assessment to record the number of falls and use of emergency health care services. The primary outcome measure will be rate of falls over the 12 month follow up period. A fall will be defined as “unintentionally coming to the ground, floor or lower level” [33] and will be recorded on monthly fall calendars which participants will receive after the baseline assessment. Both intervention and control participants will be asked to record the following details regarding falls: number of falls experienced during that month, location of the fall/s (indoor or outdoor fall) and injuries suffered. If calendars are not returned, telephone contact will be made to obtain the relevant information. This method for collection of fall information is recommended as best practice by the Prevention of Falls Network Europe (ProFaNE) [33].

### Statistical analysis

Analyses will be conducted using SPSS version 20.0 (SPSS Corp, Chicago, Ill, USA) and STATA 12 software (Stata Corp, College Station, Tex., USA). Descriptive statistics will be used to summarise demographic characteristics and baseline data. Proportion of fallers will be compared between groups using the Relative Risk statistic. Fall rates will be compared between groups using Incidence Rate Ratios (IRR) from negative binomial regression models [35]. Between-group comparisons of final EQ-5D (and other continuous measures) will be made using General Linear Models (ANCOVA) controlling for baseline performance and other confounding variables if required. Predictors of adoption and adherence will be analysed using multivariate modelling techniques. An intention-to-treat approach will be used for all between-group analyses.

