### Participant selection and identification

Community dwelling people aged 65 years or older who receive ambulance care as a result of a fall and who are considered to be appropriate (or choose) to be left at home will be invited to participate in the trial. People living in Residential Aged Care Facilities will be excluded. People living at home with a known diagnosis of dementia and no carer will also be excluded as well as those who are unable to speak and understand sufficient English to participate fully in the trial.

All referred non-conveyed older fallers will be contacted via telephone to establish that there has been no acute deterioration in their health or level of function following the fall. For falls that occur between Monday and Thursday, calls will be made within 24 hours. For falls that occur between Friday and Sunday, calls will be made on the following Monday. Once it is established that there is no requirement for emergency care, the older person will be invited to participate in a fall prevention program. If verbal consent to participation is gained then an appointment for a home visit will be offered as soon as possible.

Ethics approval has been obtained from Sydney Local Health Network Ethics Review Committee (Royal Prince Alfred Hospital Zone- Protocol No X10-0352 & HREC/10/RPAH/616) and written consent will be obtained from all eligible participants.

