### Measurement and procedures

All eligible older fallers will be visited at home by a research physiotherapist. The program will be explained in detail to participants and written consent will be obtained prior to undertaking the baseline assessment. All participants will undergo two measurements: one on entry to the study (baseline assessment) and one after the 6-month intervention period. Table 1 highlights the measures to be undertaken. At the end of the baseline assessment, the researcher will generate a list of risk factors identified and written suggestions about how they might be addressed using a template with capacity for free text to individualise advice. All pre-test measures will be assessed prior to randomisation. Post-intervention period measures will be undertaken by personnel blinded to group allocation.

**Table 1 T1:** List of measures to be collected at baseline assessment (BA) and at reassessment (RA)

	**BA**	**RA**	**O**

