**General health and function**			
Detailed information regarding non-transported fall.	✓	**✗**	**✗**
Information regarding falls and fractures in previous 12 months.	✓	**✗**	**✗**
Ambulance service use and hospitalisation in last 12 months (in general, and due to falls).	✓	**✗**	**✗**
Disease history of previous 12 months (Multipurpose Australian Co-morbidity Scoring Scale (MACSS)).	✓	**✗**	**✗**
Medication use.	✓	✓	**S**
Assistive walking device (indoor and outdoor use), need for assistance when performing seven Instrumental Activities of Daily Living (IADL).	✓	✓	**S**
The Incidental and Planned Exercise Questionnaire (IPEQ) will provide estimates of the frequency and duration of planned and incidental exercise [21].	✓	✓	**S**
Self-reported fear of falling and balance ability on a 5-point Likert-scale.	✓	✓	**S**

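### No covariate is stated for the negative binomial fall-rate model, although fall history is collected before randomisation; pre-specifying it may gain precision

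*Protocol article*

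**What the plan says.** The Outcome measures section of the protocol article states: "The primary outcome measure will be rate of falls over the 12 month follow up period". The Statistical analysis section gives the method: "Fall rates will be compared between groups using Incidence Rate Ratios (IRR) from negative binomial regression models". It compares the proportion of fallers by a relative risk. No covariate is attached to either analysis, and neither is described as adjusted or unadjusted.

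The next sentence does mention adjustment, for other outcomes: "Between-group comparisons of final EQ-5D (and other continuous measures) will be made using General Linear Models (ANCOVA) controlling for baseline performance".

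Table 1, under General health and function, lists a baseline item: "Information regarding falls and fractures in previous 12 months". Under Measurement and procedures the article adds: "All pre-test measures will be assessed prior to randomisation". The Randomisation section reads "Randomisation will be achieved using computer-generated random numbers and randomly permuted block sizes of" 4–8 and names no stratification factor.

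**The concern.** Fall counts vary widely between people, and some of that variation may be predictable from how often a person fell in the previous year. A model with treatment alone leaves all of it in the dispersion term, which widens the interval for the incidence rate ratio (IRR). With roughly 105 evaluable participants per arm and no stratification factor named, a chance excess of frequent fallers in one arm can also move the estimate.

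Fall history is measured before allocation, so treatment cannot affect it, and the paragraph that leaves the fall model without covariates gives them to secondary outcomes. What is at stake is the precision of the fall-rate comparison. Its validity is not in question.

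**Working it through.** **The plan's own figure.** The only design figure is the total of 234. It concerns proportions of fallers and contains no covariate. With 0.60 against 0.60 × 0.67 = 0.402, a one-sided 5% test, 90% power and unpooled variance:

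(1.645 + 1.282)² × (0.240 + 0.2404) / 0.198² ≈ 105 per arm; 210 / 0.9 = 233.3, rounded up to 234.

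The figure therefore reproduces, but the article does not state sidedness. That is a separate question. Here the figure supplies only the evaluable number: 234 × 0.9 / 2 ≈ 105 per arm (1:1 allocation assumed).

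**Assumptions, because the documents give no values.**
- IRR 0.67, borrowing the 33% reduction that the Sample size section states for fallers.
- Dispersion k of 0.5, 1 or 2.
- Control mean μ₀ set so that 40% of controls have no fall, matching the 60% of fallers in the Sample size section: (1 + kμ₀)^(−1/k) = 0.40. This gives μ₀ = 1.162, 1.5 and 2.625. Then μ₁ = 0.67 μ₀.
- Adjustment removes a share f of the dispersion, from 10% to 40%.

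**Formula.** Var(log IRR) = (1/105) × [1/μ₀ + 1/μ₁ + 2k(1 − f)].

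**Worked case, k = 1.** Here 1/1.5 + 1/1.005 = 1.662.
- Unadjusted: (1.662 + 2.0)/105 = 0.0349, SE 0.187.
- f = 10%: (1.662 + 1.8)/105 = 0.0330, SE 0.182, variance down 5%.
- f = 40%: (1.662 + 1.2)/105 = 0.0273, SE 0.165, variance down 22%.

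| k | Unadjusted SE | Variance reduction, f = 10% to 40% |
|---|---|---|
| 0.5 | 0.173 | 3% to 13% |
| 1 | 0.187 | 5% to 22% |
| 2 | 0.217 | 8% to 32% |

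**Simulation check.** There were 500 simulated trials per setting with 105 per arm. Negative binomial models were fitted with and without log previous falls, with k = 1 or 2 and IRR 1 or 0.67. The change in model-based variance of the log IRR was:
- history unrelated to later falls: a loss of 0.2% to 0.5%;
- correlation 0.4: a reduction of 3% to 6%;
- correlation 0.8: a reduction of 14% to 29%.

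These simulations used lognormal frailty, which the negative binomial model does not match, and rejection under no effect was 5% to 11% with or without the covariate. Only the variance ratios are therefore used.

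A second simulation with gamma frailty (k = 1, control mean 1.5, IRR 0.67, 400 runs per setting) moved the SE from about 0.187 to 0.183, 0.178 and 0.169 at correlations 0.4, 0.6 and 0.8. In variance that is 1 − (0.183/0.187)² = 4%, then 9% and 18%, inside the same range.

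**The case against.** A reader might infer from the contrast with the ANCOVA sentence that the fall-rate model is deliberately unadjusted. The article does not say so. It says nothing either way, and a condensed article commonly leaves a covariate list to the full protocol or analysis plan, neither of which is shown. The contrast also has an innocent explanation: a continuous measure repeated at follow-up has its own baseline value as the obvious covariate. This objection stands, and the point is therefore conditional on what the analysis plan contains.

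A reader might also infer that an unadjusted IRR would be biased or invalid. It would not. Chance imbalance in frequent fallers is part of the sampling error that the standard error describes.

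The covariate may be weaker than hoped. Eligible people are those "who receive ambulance care as a result of a fall", so everyone has fallen recently and history may separate them less. Table 1 does not say that an exact count is recorded, and it lists the index fall as a separate item, so whether the history includes that fall is unclear. These doubts bear on the size of the gain and on how the covariate is coded. They do not remove the case for including it.

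Two other matters should be kept apart. The phrase "controlling for baseline performance and other confounding variables if required" is open-ended, but it governs the continuous outcomes and is no evidence about the fall model. Whether 234 participants deliver the stated power is a sample-size question that adjustment neither creates nor settles.

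**Conclusion.** The point holds as a conditional improvement in efficiency and pre-specification. The article states no covariate for the fall-rate model, a suitable one is collected before randomisation, and including it is sound. With a log link in a randomised trial, adjustment leaves the IRR essentially the same quantity.

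The gain cannot be determined from the documents. Under the assumed means, dispersions and strengths of association, the variance of the log IRR falls by roughly 0% to 30%. At the upper end the interval on the log scale is about 16% narrower (1 − √0.70 = 0.16). If history does not predict later falls, the loss is at most about 0.5% of the variance. Small downside against possible gain supports the change. It does not support calling the present text wrong, or calling adjustment free.

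**What to change.** Unless the statistical analysis plan already does so, state the following before unblinding:

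- The fall-rate model contains treatment and number of falls in the previous 12 months, with log follow-up time as offset.
- The count enters as log(count + 1), or as log(count) if the index fall is included so that everyone has at least one. If no exact count was recorded, it enters in categories. Say which applies.
- A simple rule covers missing history, such as a separate missing category, so that no randomised participant is dropped for want of a baseline value.
- The unadjusted IRR is reported as a sensitivity analysis.
- The same covariate can be used for the relative risk of falling, for example in a log-link Poisson model with robust variance.

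The cost is a few sentences and one extra parameter, with the functional form and missing-data rule decided in advance. No new data are needed.

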### Economic analysis

Analysis will be undertaken in the manner used in previous fall prevention studies led by Campbell and Robertson [35,36]. The study will collect data on the cost to deliver the assessment and intervention package (including staff costs, training, capital costs and consumables), in-patient hospital admissions, ED presentations and other health and community service contact, fall rates and utility-based quality of life. Data linkage of all trial participants via CHeReL (Centre for Health Record Linkage) will be used to estimate the resource use associated with inpatient and ED visits. Incremental cost-effectiveness ratios will be calculated in terms of a) the incremental cost per fall prevented, b) the incremental cost per triple zero call avoided, c) the incremental cost per ED presentation avoided, and d) the incremental cost per hospital admission avoided and e) the incremental cost per QALY gained. Using the mean costs in the intervention and control arms, and the mean health outcomes in the control and intervention groups, the incremental cost per additional health outcome gained (outcomes a-e above) of the intervention group compared to control group will be calculated; results will be plotted on a cost-effectiveness plane. Bootstrapping will be used to estimate a distribution around costs and health outcomes and to calculate the confidence intervals around the incremental cost-effectiveness ratio. One way sensitivity analysis will be conducted around key variables, and a probabilistic sensitivity analysis will be conducted to estimate the joint uncertainty in all parameters; a cost-effectiveness acceptability curve (CEAC) will be plotted. A CEAC provides information about the probability that an intervention is cost-effective, given a decision maker’s willingness to pay for each additional health outcome.

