**Quality of life**			
The EuroQol-5D is a widely used utility-based quality of life instrument for estimating Quality Adjusted Life Years (QALYs) for economic evaluations [22]. It provides a simple descriptive profile and a single index value for health related quality of life.	✓	✓	**S**

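### The cost-per-QALY ratio is built from arm means with no baseline adjustment named; adjusting QALYs for baseline EQ-5D would gain precision and remove chance imbalance at no cost

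*Protocol article*

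**What the plan says.** In the protocol article, the Economic analysis section lists five ratios, the last being "e) the incremental cost per QALY gained". One rule then covers all five. It starts from "Using the mean costs in the intervention and control arms, and the mean health outcomes in the control and intervention groups", and from these "the incremental cost per additional health outcome gained (outcomes a-e above) of the intervention group compared to control group will be calculated". No covariate or model is named. For uncertainty, "Bootstrapping will be used to estimate a distribution around costs and health outcomes"; one-way and probabilistic sensitivity analyses and an acceptability curve follow.

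The Statistical analysis section treats the same instrument differently: "Between-group comparisons of final EQ-5D (and other continuous measures) will be made using General Linear Models (ANCOVA) controlling for baseline performance".

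Table 1 (Quality of life) describes the EQ-5D as a "utility-based quality of life instrument for estimating Quality Adjusted Life Years (QALYs) for economic evaluations" and ticks it at baseline and at reassessment. Under Measurement and procedures there are two measurements, "one on entry to the study (baseline assessment) and one after the 6-month intervention period", and "All pre-test measures will be assessed prior to randomisation". The article does not say how EQ-5D values become QALYs.

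**The concern.** Outcomes (a) to (d) are events counted after randomisation. A QALY need not be like that. If it is the area under the EQ-5D curve from baseline, the pre-randomisation utility is part of the outcome. Two people who do not change, one at 0.80 throughout and one at 0.60 throughout, would score 0.40 and 0.30 QALYs over 6 months. That is a difference of 0.10 with no change in either person.

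EQ-5D is measured before allocation, so a baseline difference between the arms is chance. On the plain reading of the arm-means rule, that chance difference passes into the QALY difference and so into the ratio, the cost-effectiveness plane and the acceptability curve. The clinical EQ-5D comparison removes it. The two analyses of the same data could then point in different directions, and the economic one would be the noisier.

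**Working it through.** The plan states no QALY figure to reproduce. Its sample size is used only to set the arm size.

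**Inputs**
- From the Sample size section: 234 in total, 10% dropout. 234/2 = 117 per arm; 117 × 0.9 = 105.3, taken as n = 105.
- Assumed, not in the documents: EQ-5D SD σ = 0.25 (range 0.20 to 0.30), correlation ρ between baseline and 6 months = 0.6 (range 0.4 to 0.7), true utility gain at 6 months = 0.05.
- Assumed QALY form: Q = w0·u0 + w6·u6, with u0 and u6 the baseline and 6-month utilities. Area under the curve over 6 months gives (w0, w6) = (0.25, 0.25). Carrying the 6-month value to 12 months gives (0.25, 0.75).

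**Size of a chance imbalance.** The SE of the baseline difference is σ√(2/n) = 0.25 × √(2/105) = 0.0345 (0.0276 at SD 0.20, 0.0414 at SD 0.30).

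**How much reaches the QALY difference.** Given a baseline difference D, the expected spurious QALY difference is (w0 + w6·ρ)·D. For D = 0.0345:
- 12 months: (0.25 + 0.75 × 0.6) × 0.0345 = 0.0242, against a true effect of 0.75 × 0.05 = 0.0375.
- 6 months: (0.25 + 0.25 × 0.6) × 0.0345 = 0.0138, against a true effect of 0.25 × 0.05 = 0.0125.

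**Precision.** The unadjusted variance of Q is σ²(w0² + w6² + 2·w0·w6·ρ). After regression on u0 it is σ²·w6²·(1 − ρ²). The SE of the arm difference is √(2·variance/n).

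| Horizon | SE unadjusted | SE adjusted | Variance ratio | Wrong sign, unadjusted | Wrong sign, adjusted |
|---|---|---|---|---|---|
| 12 months, carried forward | 0.0318 | 0.0207 | 0.85/0.36 = 2.36 | Φ(−0.0375/0.0318) = 12% | Φ(−0.0375/0.0207) = 3.5% |
| 6 months only | 0.0154 | 0.0069 | 0.20/0.04 = 5.0 | Φ(−0.0125/0.0154) = 21% | Φ(−0.0125/0.0069) = 3.5% |

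The simulated SDs of the difference agree: 0.0316 and 0.0206 over 12 months, 0.0153 and 0.0069 over 6 months.

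**Range.** The variance ratio does not depend on σ or n. For ρ from 0.4 to 0.7 it is 1.6 to 3.1 over 12 months and 3.3 to 6.7 over 6 months. The 12-month wrong-sign rate, over σ 0.20 to 0.30 and ρ 0.4 to 0.7, is 6% to 17% unadjusted and 1% to 9% adjusted.

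**Other QALY formulas**
- Only the 6-month value used (w0 = 0): the ratio is 1/(1 − ρ²) = 1/0.64 = 1.56, because imbalance still acts through ρ.
- Change from baseline over 12 months, (w0, w6) = (−0.75, 0.75): the carry-over is (−0.75 + 0.45) × 0.0345 = −0.0104, in the opposite direction, and the ratio is 0.45/0.36 = 1.25.
- In every case, regressing Q on arm and u0 removes the w0·u0 term exactly. The adjusted QALY difference is then w6 times the baseline-adjusted EQ-5D difference, so with the same participants and covariates the two analyses agree by construction.

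**The case against.** The strongest case against has five parts.

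- **The text does not call the means raw or unadjusted.** ANCOVA also yields arm means, and a participant's QALYs might count among the continuous measures to be adjusted. This stands in part. Unadjusted means are the plain reading of one rule that covers event counts and QALYs alike, but they are not stated.
- **The QALY formula above is supplied here, not by the article.** This stands. The formula sets the size and even the direction of the carry-over. It does not decide whether adjustment helps: each form tried gains from it.
- **The section says it follows earlier fall-prevention studies, and an article leaves detail to fuller documents.** Those studies are not shown and might adjust. But the article does state how the ratio is formed, so the point concerns a stated rule, not a missing detail.
- **Randomisation makes the unadjusted estimate unbiased, and the bootstrap displays its uncertainty.** Both are true. Resampling unadjusted means still leaves the estimate centred on the imbalance drawn and gives a wider interval than the data require.
- **The 6-month figures flatter the concern, since evaluation runs for 12 months.** This stands, and the 12-month figures should lead.

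A reader might infer that the two analysis sections contradict each other, or that the cost-per-QALY ratio is biased. The documents support neither. One section concerns final EQ-5D and the other an incremental ratio, so they are different quantities, and the estimator is valid over repeated randomisation.

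**Conclusion.** The point holds as an efficiency improvement. On its plain reading, the plan leaves the QALY difference unadjusted for a baseline measure that it collects and uses for adjustment elsewhere. Under the stated assumptions the avoidable loss is a variance about 2.4 times larger over 12 months, or about 5 times over a 6-month horizon. These sizes rest on an assumed SD, correlation, utility gain and QALY formula, none of which the documents give, so they are illustrative. That adjustment helps depends on much less: EQ-5D at 6 months must be correlated with its baseline, or the QALY formula must include the baseline value.

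The reach is limited to ratio (e). Ratios (a) to (d), the falls outcome and the clinical EQ-5D comparison are untouched.

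**What to change.** In the Economic analysis section, state that the QALY difference for ratio (e) comes from a regression of each participant's QALYs on arm and baseline EQ-5D index. Refit it in every bootstrap replicate, with costs resampled from the same participants, so that the plane and the acceptability curve use the adjusted difference. Report the unadjusted difference as a sensitivity analysis. State the QALY formula in the same sentence, and fix all of this before outcomes are seen by arm.

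The cost is one or two sentences and one regression per replicate. No new data, visits or participants are needed, because EQ-5D is already scheduled before randomisation. If adjustment is already intended, saying so is enough.

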**Follow-up- 12 months**			
Falls (monthly diaries) [33].			**P**
Subsequent use of health services (differentiation between fall-related or other medical reason) collected from monthly diary and with further telephone call for clarification if required.			**S**
GP visit, Specialist medical practitioners visit, ambulance service use, ED presentation, hospital admission, physiotherapy, occupational therapy.			
Number of falls requiring ED attendance and/or hospitalisation collected from monthly diary and with further telephone call for clarification if required.			**S**
Use of NSW Ambulance Service, including time on scene (routinely collected Ambulance Service data).			**S**
Any ED presentation or hospitalisation including Diagnosis Related Group (DRG) and Length of Stay (LOS) data (measured using falls calendar data and corroborated through the NSW Admitted Patient Data Collection).			**S**
Use of any community health services – GP visits, Home medication review (HMR), Aged Care Assessment Team (ACAT) referrals, use of Post Acute Care Service (PACS) services etc. (measured using monthly falls calendar data).			**S**
Uptake and adherence to recommendations (based on initial and post-intervention assessments).	**✗**	✓	**S**

*BA* Baseline Assessment, *RA* Reassessment, *O* Outcome measure, *S* secondary, *P *Primary.

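### Incremental cost is taken from the two arm means with no covariate, although prior-year ambulance and hospital use is recorded at baseline; adjusting for it would gain some precision at almost no cost

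*Protocol article*

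**What the plan says.** The Economic analysis section describes the cost comparison in these words: "Using the mean costs in the intervention and control arms, and the mean health outcomes in the control and intervention groups". Five ratios follow (per fall prevented, triple zero call avoided, ED presentation avoided, admission avoided and QALY gained), all with the same cost numerator. On uncertainty it says: "Bootstrapping will be used to estimate a distribution around costs and health outcomes and to calculate the confidence intervals around the incremental cost-effectiveness ratio". Neither sentence names a covariate.

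Table 1, under General health and function, lists the item "Ambulance service use and hospitalisation in last 12 months (in general, and due to falls" as collected at baseline only. Measurement and procedures places all baseline measures before randomisation.

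The Statistical analysis section takes a different line for other outcomes: "Between-group comparisons of final EQ-5D (and other continuous measures) will be made using General Linear Models (ANCOVA) controlling for baseline performance". It adds further confounders where required and does not mention cost.

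On allocation, the Randomisation section says: "Randomisation will be achieved using computer-generated random numbers and randomly permuted block sizes of 4–8". It mentions no stratification by prior service use.

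**The concern.** A person's past use of ambulance and hospital is a natural predictor of later use, and so of later cost. The article itself describes a population with frequent repeat use: in the New South Wales study cited in the Background, 27% called an ambulance again because of a fall within 6 months. That is evidence about the population. It does not show how strongly use persists within a person, but it makes prior use a credible covariate.

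The trial collects this predictor, does not report balancing it by design, and does not name it in the cost analysis. It does adjust EQ-5D and other continuous measures for baseline. If cost counts as one of those measures, the two sections should be reconciled. If it does not, cost is compared without a baseline predictor that is already on file. At stake is the width of the interval around the cost numerator that all five ratios share.

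**Working it through.** **Inputs from the protocol article.** Total sample 234, power 90%, significance level 5%, dropout 10% (Sample size); follow-up 12 months (Outcome measures). The allocation ratio is not stated, so 1:1 is assumed: 117 per arm randomised. The documents give no mean or SD of cost, so shifts are expressed in SDs of cost. They give no correlation r between prior use and follow-up cost, so r is assumed over 0.1 to 0.6.

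**The plan's own figure.** The plan states no precision for cost. Its only figure used here is 234, as the sample size. With 60% against 60% × 0.67 = 40.2%, unpooled variance and a one-sided 5% test at 90% power, the formula gives 105 per arm, and 210/0.9 = 233.3, or 234 after rounding up to equal arms. A two-sided 5% test does not reproduce it. That is a separate matter and does not affect this point. The two sizes used below are 117 and 105 per arm.

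**Step 1: precision.** Linear adjustment multiplies the variance of the cost difference by 1 − r² and the interval width by √(1 − r²). The equivalent unadjusted sample is 234/(1 − r²).

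| Assumed r | Variance factor | Interval narrower by | Equivalent total N |
|---|---|---|---|
| 0.1 | 0.99 | 0.5% | 236 |
| 0.2 | 0.96 | 2% | 244 |
| 0.3 | 0.91 | 5% | 257 |
| 0.5 | 0.75 | 13% | 312 |
| 0.6 | 0.64 | 20% | 366 |

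**Step 2: chance imbalance.** The difference between arms in standardised prior use has SD √(2/117) = 0.131, so its 95% range is ±1.96 × 0.131 = ±0.26. It moves the unadjusted cost difference by r × 0.26: about 0.05 cost SD at r = 0.2, 0.08 at 0.3 and 0.13 at 0.5. With 105 per arm the SD is √(2/105) = 0.138 and the shifts are 0.05, 0.08 and 0.14. The unadjusted cost difference itself has a standard error of √(2/117) = 0.131 cost SD, so the SD of the shift is r times that standard error. It is already part of the sampling error that the interval covers.

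**Step 3: check with skewed cost.** A simulation used lognormal prior use and cost, 105 per arm, no treatment effect and 5,000 runs. The mean error of the unadjusted difference was between −0.004 and 0.0005, against an SD of about 0.51. Its 95% interval (mean ± 1.96 standard errors; the bootstrap itself was not simulated) covered 95% to 96%. Adjustment cut the SD of the estimate by 2%, 8% and 19% for target correlations of 0.2, 0.3 and 0.5. The sample correlations averaged 0.22, 0.33 and 0.53.

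**Step 4: an illustration in money, all values assumed.** Take 0.8 admissions per person-year, dispersion 1.5, A$8,000 per admission and 105 per arm. The variance per person is 0.8 + 1.5 × 0.8² = 1.76, and the standard error of the arm difference is √(2 × 1.76/105) = 0.183 admissions, or 0.183 × 8,000 = about A$1,460. If individual risk persists fully, the slope of follow-up on prior admissions is 0.96/1.76 = 0.545. A one-standard-error imbalance then carries 0.545 × 1,460 = about A$800 per person into the cost difference, and about A$400 at half persistence. That is 0.55 and 0.27 of one standard error.

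**The case against.** The strongest reply is that the plan is valid as written. A difference in arithmetic mean cost is unbiased under randomisation, and the planned bootstrap allows for chance imbalance. This stands, and Steps 2 and 3 support it. What remains is a matter of efficiency.

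Second, the article does not say that the means are unadjusted. It says mean costs in the arms, refers to the manner of earlier fall prevention studies that are not at hand, and elsewhere allows adjustment of continuous measures: "will be made using General Linear Models (ANCOVA) controlling for baseline performance and other confounding variables if required". This stands in part. Adjusted means are not excluded, but unadjusted means are the natural reading, and a covariate used only if required is not fixed in advance.

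Third, the gain rests on an unknown correlation. Prior ambulance use and hospitalisation also say little about GP, community service or programme delivery costs, which lowers r for total cost. This stands too, and is why a range is shown.

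A reader might go further and infer three things that the documents do not support:

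- **That chance imbalance biases the cost result.** It does not; it is sampling error.
- **That a few heavy prior users could decide the sign of the incremental cost.** The illustration puts the carry-over at 0.27 to 0.55 of one standard error, which does not show this.
- **That the plan compares ambulance, ED and admission counts without adjustment.** The only count model stated is for falls: "Fall rates will be compared between groups using Incidence Rate Ratios (IRR) from negative binomial regression models". For service-use counts no model is given, adjusted or not, and a condensed article may leave that to the analysis plan.

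**Conclusion.** The point holds as a modest improvement to the cost comparison only. The stated estimator is sound but leaves out a baseline predictor that the trial collects. The gain is negligible if r is 0.2 or less, about 5% of interval width at 0.3 and 13% at 0.5. This assumes 1:1 allocation, a roughly linear relation, and a correlation that the documents do not supply. It is not an error in the plan, and neither the validity of the ratios nor the direction of the result is in question.

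**What to change.** In the Economic analysis section, state that incremental cost will be estimated from a linear regression of 12-month cost on arm plus prior 12-month ambulance use and hospitalisation, refitted in each bootstrap replicate. Cost and effect should come from the same resample, so that their correlation is kept. The estimate is still a difference in mean cost. Report the unadjusted arm means alongside as a sensitivity analysis.

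Heavy prior users have high leverage in such a model, so prior use may be entered in capped or categorised form. The form should be fixed before the outcome data are seen.

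The cost is a sentence or two of wording and a few lines of code. No new data are needed, and sample size and visits are unchanged.
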